##### TCM symptom score

The TCM symptom score for patients with stable COPD diagnosed with deficiency of lung qi and spleen qi will be adopted. The TCM symptom score scale is scored from 0 (normal) to 22 (severe). The TCM symptom score is shown in Table 2.

**Table 2 Tab2:** TCM symptom score

Main symptom (score)	Normal (0)	Light (2)	Medium (4)	Severe (6)
Cough	No	Intermittent cough during the day	Cough during day and night without affecting work and sleep	Cough frequently during day and night which affects work and sleep
Sputum	No	A small amount of sputum	Sputum and wheezy phlegm	A large amount of sputum and loud wheezy phlegm
Shortness of breath	No	Shortness of breath after work	Fatigue and shortness of breath	Short of breath when quiet
Secondary symptoms	Normal (0)	Light (1)	Medium (2)	Severe (3)
Spontaneous perspiration	No	Sweat while eating	Intermittent sweat	Sweat soaks clothes, sweat more after work
Loss of appetite	No	Loss of appetite, but eat as usual	Eat less but not under one-third of usual	Eat less than one-third of usual
Weak	No	Can do light physical work	Can’t do physical work	General fatigue, intend to stay in bed
Abdominal distention and loose stool	No	Light abdominal distention and the stool is not forming	Abdominal distention is obvious and loose stool	Abdominal distention is obvious and water-like stool

##### Lung function

Forced vital capacity (FVC), forced expiratory volume in 1 s (FEV1), forced expiratory volume in 1 s (FEV1% pred), FEV1/FVC, maximum expiratory mid-flow (MMEF), and peak expiratory flow (FEF) will be tested. A positive change from baseline in these will indicate an improvement in lung function.

The Modified Medical Research Council (MMRC) scale by the American Thoracic Society [17] will be assessed to evaluate the level of dyspnea. The MMRC scale is a simple grading system that scores from 0 (less severe) to 4 (severe).

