### Main outcome measures

The primary outcome is frequency of AECOPD. The secondary outcomes are duration of AECOPD, TCM symptom score, lung function, COPD Assessment Test (CAT) score, Modified Medical Research Council (MMRC) grade, BODE (Body mass index, airflow Obstruction, Dyspnea and Exercise capacity) score, and 6-min walking distance .

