### Screening and run-in, baseline, treatment periods, and endpoint

Adverse events, physical examination, AECOPD situation and MMRC, CAT, and TCM symptom scores will be recorded at baseline (week 0) and every 4 weeks during the study period. The 6-min walking distance and BODE will be recorded at weeks 0, 4, 12, 24, 32, and 52. Lung function will be observed at weeks 0, 24, and 52. Safety will be measured at weeks 0, 12, and 24, not including adverse events and the physical examination. The schedule of assessments and interventions is depicted in Fig. 2.

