### Statistical analysis

All data will be analyzed by an independent statistician using SAS 9.4. For all analyses, *P* < 0.05 is considered statistically significant. Measurement data will be presented as number of cases, mean, standard deviation, minimum, median, maximum, upper quartile (Ql), lower quartile (Q3), and 95% confidence interval (95% Cl) data. Paired-sample *t*-test or signed rank sum test will be used to compare the difference between the two groups or pretreatment and posttreatment within one group. Analysis of covariance will be used to compare the differences of center effector other confounding factors.

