In our study, the frequency of acute AECOPD has been chosen as the primary outcome. We also employ validated and objective tools, such as the ACT score and FEV1, as outcome measurements. These measurements improve the reliability and generalizability of the results. Measures will be taken to strengthen quality control. To avoid bias from researchers during this study, an investigator separate from all of the clinical researchers will be hired to preserve and record the randomization information. Therefore, the clinical researchers will not have any input to enrollment or randomization. Also, outcome assessments will be made by an independent clinical statistician blinded to group allocation and not involved in providing intervention or management. We have built a TCM symptom score table to evaluate the TCM symptoms of patients with stable COPD diagnosed with deficiency of lung qi and spleen qi. However, considering the difficulty of recruitment because of the strict inclusion criteria, we have adopted the minimum sample size. Thus, the sample size is a little too small to observe changes in lung function and then show an effect of SHGBZK treatment.

The study has been developed according to the Consolidated Standards of Reporting Trials (CONSORT) [17] statement.

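### A rise from baseline is read as improvement for all six spirometry values, which is invalid for FEV1/FVC and names no placebo comparator

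*Protocol article*

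**What the plan says.** Under Secondary outcome measures, the Lung function section names FVC, FEV1 and FEV1 as a percentage of predicted, and continues: "FEV1/FVC, maximum expiratory mid-flow (MMEF), and peak expiratory flow (FEF) will be tested". The next sentence gives one reading for all six: "A positive change from baseline in these will indicate an improvement in lung function". It makes no exception for the ratio, states no size of change and mentions no comparator.

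Four other places bear on how that sentence would be used:

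- **Main outcome measures** makes lung function secondary: "The secondary outcomes are duration of AECOPD, TCM symptom score, lung function, COPD Assessment Test (CAT) score".
- **Screening and run-in, baseline, treatment periods, and endpoint** sets the timing: "Lung function will be observed at weeks 0, 24, and 52".
- **Statistical analysis** describes continuous data by summary statistics ("Measurement data will be presented as number of cases, mean, standard deviation, minimum, median, maximum") and names t or signed rank tests that "will be used to compare the difference between the two groups or pretreatment and posttreatment within one group". A P value below 0.05 "is considered statistically significant". Analysis of covariance is named for centre effects and other confounders.
- **Discussion** concedes that "the sample size is a little too small to observe changes in lung function".

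**The concern.** Two separate faults lie in the one sentence.

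First, five of the six values are volumes, flows or a rescaled volume, for which higher is better in the sense the sentence intends. FEV1/FVC is a quotient. It goes up when its numerator rises or when its denominator falls, and the sentence treats both as improvement. A loss of FVC could then be reported as a gain in lung function.

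Second, the sentence rests on change from baseline. Both arms receive basic COPD treatment, so a rise within the herbal arm cannot by itself be credited to the herbal formula. The Statistical analysis section does not settle the matter, because it permits a pre/post test within one group as well as a test between groups and does not rank them. At stake is a lung-function statement in the final report that rests on the ratio alone, or on a within-arm rise alone, and that still agrees with the protocol.

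**Working it through.** The protocol gives no figure for lung function (no threshold, standard deviation or power), so there is no stated number to reproduce. The litre values below are illustrative and are not taken from the document.

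**1. When the ratio rises.** Let FEV1 fall by a fraction a and FVC by a fraction b. The new ratio is the old ratio × (1 − a)/(1 − b). It rises exactly when b > a, whatever happens to FEV1 itself.

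**2. Both volumes fall, ratio rises.** FEV1 goes from 1.50 to 1.40 L, so a = 0.10/1.50 = 6.7%. FVC goes from 3.00 to 2.60 L, so b = 0.40/3.00 = 13.3%.
- Before: 1.50/3.00 = 0.500.
- After: 1.40/2.60 = 0.538.

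The protocol's sentence calls this an improvement.

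**3. Both volumes rise, ratio falls.** FEV1 goes from 1.20 to 1.30 L and FVC from 2.40 to 2.80 L.
- Before: 1.20/2.40 = 0.500.
- After: 1.30/2.80 = 0.464.

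The sentence gives no credit here although both volumes improved. The direction can therefore mislead either way.

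**4. Arm level.** Suppose the average FEV1 in one arm falls from 1.50 to 1.47 L and the average FVC from 3.00 to 2.85 L. The quotient of the averages goes from 1.50/3.00 = 0.500 to 1.47/2.85 = 0.516. (A mean of individual ratios is not identical to a ratio of means, but it responds to FVC in the same way.) If the other arm stayed at 0.500, the between-arm contrast in the ratio would be 0.516 − 0.500 = +0.016 in favour of the arm that had lost both volumes. So a between-arm comparison does not by itself cure the ratio problem; the ratio has to be read beside its two components.

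**5. Comparator.** Set the two sections side by side. The Lung function section defines improvement by change from baseline. The Statistical analysis section offers between-group and within-group tests joined by "or", with no statement of which carries the conclusion. The wording of the first section fits the within-group test, and nothing in the second excludes that use.

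**The case against.** The strongest defence is that the sentence only states a direction. The neighbouring sections do the same for their own scales: higher CAT and BODE scores mean a worse state, for example. Spirometry runs the other way, so the article says so. The planned analysis uses means, confidence intervals and tests, and includes a comparison between randomised groups. FEV1 and FVC are measured at the same visits as the ratio, so a fall in both would be visible. The choice of a lead parameter and of covariates is ordinarily left to the analysis plan.

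Much of this stands, and it rules out three stronger readings that a reader might infer.

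- *Noise alone meets the rule in most patients.* With no true change and symmetric error, the chance of a rise is 50% for a single value, which is not most. Larger figures need a rule that one rise out of six is enough: 98% if the six are independent, and 92% to 66% at assumed common correlations of 0.3 to 0.9. The article states no such rule. If all six had to rise, the figure would be about 2% under independence and 34% at a correlation of 0.9.
- *Patients are classed as improved on any of six values.* No section defines a responder or a proportion improved.
- *The whole lung-function conclusion is uninterpretable.* In a between-arm comparison, test-retest noise falls on both arms alike and adds variance, not bias. A between-arm result for FEV1 remains readable. The Discussion's remark on sample size is an open limitation, not evidence that any rise will be called benefit.

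The defence does not rescue the sentence for the ratio. Even as a plain statement of direction, higher is better is not true of FEV1/FVC taken alone. Nor is this detail left to another document: the article fixes an interpretation, and an analysis plan that handled the ratio properly would depart from it.

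**Conclusion.** The point holds in a limited form. The rule that a positive change means improvement is invalid for one of the six listed values, FEV1/FVC, for patients and for arm averages alike. It is also worded without a placebo comparator, and the Statistical analysis section leaves open whether a within-group or a between-group result decides benefit.

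The ratio argument is algebra and needs no assumption about the trial's data; only the litre values are illustrative. How often the ratio and the volumes would disagree in this trial cannot be derived from the article, which gives no spirometry means, standard deviations or correlations.

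Severity is minor. Lung function is secondary, and the primary outcome, its test and the sample size are unaffected.

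**What to change.** Replace the sentence in the Lung function section with one to this effect: benefit on lung function is judged on the difference between arms in FEV1 at weeks 24 and 52, adjusted for baseline FEV1 and given with its 95% confidence interval; FVC, FEV1 % predicted, MMEF and peak flow are supportive; FEV1/FVC is not read as improvement on its own, but only together with the FEV1 and FVC results.

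In the Statistical analysis section, add that pre/post tests within one group are descriptive for lung function and do not establish benefit.

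The cost is a sentence in each section. The spirometry and its schedule stay as they are, and analysis of covariance is already among the named methods. The downside is that fewer parameters can be claimed as improved. The Discussion's caveat about sample size should stay, since this change does not add precision.

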##### Quality of life

The COPD Assessment Test (CAT) will be adopted. The CAT is a self-complete questionnaire with eight items, each formatted as a 6-point semantic differential scale ranging from 0 to 5. CAT scores range from 0 to 40. Higher scores denote a more severe impact on a patient’s quality of life. The patients will be invited to complete the questionnaires through face-to-face survey. The patients can answer each question and check the most appropriate opinion (a specific score) with regards to their standards, hopes, pleasures, and concerns. Meanwhile, an investigator in each center will be assigned in the office to help the patients and to check through each completed questionnaire to ensure that the patients have answered all the questions.

##### The 6-min walking distance

The 6-min walking distance is used to evaluate the distance a person can walk on a flat surface in 6 min to assess their exercise capacity. The BODE index will be used; BODE stands for Body mass index, airflow Obstruction, Dyspnea and Exercise capacity. BODE scores range from 0 to 40 and will be further quartilized as follows: quartile 1 (a score of 0 to 2 points), quartile 2 (a score of 3 to 4 points), quartile 3 (a score of 5 to 6 points), and quartile 4 (a score of 7 to 10 points). The higher the level, the worse the patient’s condition.

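### The BODE score is to be cut into four unequal fixed bands, and the article does not say whether the score or the band is compared between arms; if it is the band, power is lost.

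*Protocol article*

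**What the plan says.** Under Main outcome measures, the protocol article lists the secondary outcome as "BODE (Body mass index, airflow Obstruction, Dyspnea and Exercise capacity) score", that is, a score.

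Under Secondary outcome measures, in the part headed The 6-min walking distance, it gives BODE a range of 0 to 40 and says that the scores "will be further quartilized as follows: quartile 1 (a score of 0 to 2 points), quartile 2 (a score of 3 to 4 points"), then "quartile 3 (a score of 5 to 6 points), and quartile 4 (a score of 7 to 10 points"). The only rule for reading the result comes next: "The higher the level, the worse the" patient's condition.

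Under Screening and run-in, baseline, treatment periods, and endpoint, the visits are fixed: "The 6-min walking distance and BODE will be recorded at weeks 0, 4, 12, 24, 32, and 52".

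The Statistical analysis section gives methods for measurement data in general: a t-test or signed rank test, and analysis of covariance for centre or other confounding factors. It has no rule specific to BODE. No section says that the band replaces the score in the between-group comparison, and none says that it does not.

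**The concern.** The banding appears in the definition of an outcome and is worded as something that will be done to the data. The article gives ranges for the TCM symptom score, the MMRC grade and the CAT, but does not group those totals; BODE alone is cut. The name of the outcome points to the score, while the definition and its reading rule point to the level. Both a numeric and a four-level analysis therefore fit the text, and the choice could be made after the data are seen.

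The two choices are not equivalent. Banding discards movement inside a band and counts a small movement across an edge as a full level. The result then depends on where patients start relative to the cut points. With 50 patients per arm, or 40 after the planned dropout, a modest real difference on BODE could be missed for that reason alone.

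The word quartile is also misleading. Quartiles of this sample would hold about 100/4 = 25 patients each. Fixed cut points promise nothing of the kind.

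**Working it through.** **Plan figure to reproduce.** There is none for BODE. The only sample-size calculation concerns exacerbation frequency and does not bear on this point. From it I take only the arm sizes: 50 enrolled and 40 after 20% dropout (50 × 0.80 = 40), with two-sided alpha 0.05.

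**Step 1: range against bands.** The bands 0–2, 3–4, 5–6 and 7–10 hold 3 + 2 + 2 + 4 = 11 score values. The stated range of 0 to 40 holds 41, so 41 − 11 = 30 values (11 to 40) would have no band. The article gives the same 0 to 40 range for the CAT. The remaining steps use 0 to 10, the span that the bands cover.

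**Step 2: one-point steps.** Between 0 and 10 there are 10 adjacent steps. Only 2–3, 4–5 and 6–7 cross an edge, so 3 of 10 change the band and 7 of 10 do not. A three-point fall from 10 to 7 counts as no change, while a one-point fall from 5 to 4 counts as a full level.

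**Step 3: power, if the band is compared.** The article gives no BODE mean, SD or effect, so all of these are assumed:
- baseline mean 3, 4, 5 or 6; baseline SD 1.5, 2.0 or 2.5; SD of change 0.75, 1.0 or 1.5;
- scores rounded to whole points and limited to 0–10; 40 or 50 per arm; 3,000 simulated trials per scenario;
- effect set for about 80% power on the score: effect = (1.96 + 0.84) × SD × √(2/n).

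For change, SD = √(SD of change² + 1/6), where 1/6 allows for rounding two scores. For the follow-up-only test, SD = √(baseline SD² + SD of change² + 1/12).

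Example with n = 50, mean 4, baseline SD 2.0 and SD of change 1.0:
- change and ANCOVA: SD = √(1 + 1/6) = 1.08; effect = 2.80 × 1.08 × 0.20 = about 0.61 points;
- follow-up only: SD = √(4 + 1 + 1/12) = 2.25; effect = 2.80 × 2.25 × 0.20 = 1.26 points.

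| Analysis (example) | Power on score | Power on band |
|---|---|---|
| t-test on change | 76% | 53% |
| ANCOVA, baseline-adjusted | 76% | 55% |
| t-test on follow-up only | 79% | 76% |

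In this example 57% of one-point changes leave the band unchanged.

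Across all scenarios:

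| Analysis | Power lost by banding (points) | Median |
|---|---|---|
| t-test on change | 13 to 34 | 24 |
| ANCOVA, baseline-adjusted | 11 to 33 | 22 |
| t-test on follow-up only | 3 to 10 | 5 |

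Between 52% and 66% of one-point changes stay inside a band. The follow-up-only figures belong to a larger assumed effect, because that test needs one to reach the same power.

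**Step 4: other assumptions.** A second simulation used baseline mean 3 to 5, SD 2, a correlation of 0.7 to 0.9 between baseline and follow-up, 40 or 50 per arm, and 1,500 trials per scenario. ANCOVA power was 74–79% on the score and 46–69% on the band, a loss of about 10 to 27 points. The t-test on change gave 67–76% and 43–61%, a loss of about 11 to 30 points.

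**Step 5: if the numeric score is compared.** The score is not altered, so the loss is 0.

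**The case against.** The strongest reply is that the plan never says the bands are tested. The outcome is named as a score, and a further grouping reads naturally as an addition to the score, not a replacement. The Statistical analysis section lists means, t-tests, rank tests and covariance analysis, which suit a numeric score at least as well as four levels, and it names no method specific to ordered categories. The sentence on higher levels may only give direction, as a similar sentence does for the CAT. Which form of BODE is tested could be left to an analysis plan that is not shown.

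Much of this stands. A reader might infer that the trial will compare bands and so will lose 10 to 30 points of power. The documents do not support that: the loss is conditional on a choice that the article leaves open. Nor is the size a property of this trial, since every mean, SD and effect behind it is assumed. It is also much smaller for a follow-up-only comparison, which the general wording of the analysis section does not exclude.

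The consequence is limited as well. Exercise capacity, lung function and dyspnoea each have their own secondary outcome in the 6-min walking distance, lung function tests and MMRC grade.

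The reply does not remove the stated step itself. The article goes beyond silence: it fixes cut points for an outcome, calls them quartiles and interprets the resulting level, next to a range that the cut points do not cover.

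**Conclusion.** The point holds in conditional form. It is firm, from the text alone, that the bands are unequal, that they are fixed cuts and not sample quartiles, that 7 of 10 one-point steps leave the band unchanged, and that the stated range contradicts the bands. It is also firm that the article does not say which form of BODE is compared.

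The power cost applies only if the bands are compared. It is then about 10 to 34 points for change or baseline-adjusted analyses and about 3 to 10 points for a follow-up-only comparison, under the assumed inputs above and with power on the score of roughly 70 to 80% (67% at the lowest). The matter concerns one secondary outcome among several. The primary outcome and its sample size are untouched, so this is a cheap improvement and not a threat to the trial's main conclusion.

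**What to change.** In the BODE text under The 6-min walking distance:
- state that the between-group comparison uses the full numeric BODE score, adjusted for baseline BODE;
- keep the four bands for describing patients and for a supportive table, without a test, and call them categories instead of quartiles;
- reconcile the range of 0 to 40 with bands that end at 10, after checking it against the scoring rule in use.

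This takes two or three sentences. It needs no new data or visits, because the score must be calculated before it can be banded. The one drawback is that the headline BODE result becomes a mean difference in points and not a shift between named bands; the supportive table still shows the shift.

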##### Concomitant medication status

Drug therapies used to treat COPD during the study will be recorded.

##### Mortality

All-cause mortality and COPD mortality will be calculated for the subjects during the study.

##### Safety

Routine blood, urine, and stool tests, liver and kidney function tests, and an electrocardiogram will be performed. Adverse events will be recorded at any time during the treatment period and follow-up period.

Adverse events will be recorded and graded in detail throughout the study, such as possible side effects (no side effects of the herbs have been reported so far). If a severe adverse event occurs, participants will be provided with every necessary treatment, and the event must be reported to the leader of the trial, ethics committees, sponsors, and China Food and Drug Administration (CFDA) within 24 h.

### Screening and run-in, baseline, treatment periods, and endpoint

Adverse events, physical examination, AECOPD situation and MMRC, CAT, and TCM symptom scores will be recorded at baseline (week 0) and every 4 weeks during the study period. The 6-min walking distance and BODE will be recorded at weeks 0, 4, 12, 24, 32, and 52. Lung function will be observed at weeks 0, 24, and 52. Safety will be measured at weeks 0, 12, and 24, not including adverse events and the physical examination. The schedule of assessments and interventions is depicted in Fig. 2.

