### Design and setting

One-hundred patients with stable COPD are randomly assigned to two treatment groups (SHGBZK Chinese medicine treatment, *N* = 50; placebo treatment, *N* = 50). The two groups will receive basic treatment for COPD according to the 2017 GOLD Guidelines for Chronic Obstructive Pulmonary Disease. Both groups will receive a 24-week intervention and patient status is assessed at 24 weeks and then 28 weeks after treatment.

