### Withdrawal, dropout, and discontinuation

Participants are free to withdraw at any time during the trial. Participants who wish to withdraw will be offered the option to cease trial medication but continue attending scheduled visits for outcome measurement. Participants who withdraw will be followed to investigate the reason for withdrawal. Participants may be advised to discontinue the treatment if there is a product-related adverse event of a serious nature or if the participant was not compliant with the study requirements. Discontinuers will not be replaced by new participants. Intention-to-treat analysis will be performed on missing data from discontinuers with the last observation carried forward method.

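### CAT, MMRC and TCM symptom scores are measured every 4 weeks, but none of the stated methods analyses the repeated values together, and discontinuers' gaps are filled by last observation carried forward

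*Protocol article*

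**What the plan says.** **Schedule.** Under Screening and run-in, baseline, treatment periods, and endpoint, the protocol article states that "AECOPD situation and MMRC, CAT, and TCM symptom scores will be recorded at baseline (week 0) and every 4 weeks during the study period". Design and setting adds that "patient status is assessed at 24 weeks and then 28 weeks after treatment", which means weeks 24 and 24 + 28 = 52.

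**Methods.** Statistical analysis names a paired-sample t-test or a signed rank sum test to "compare the difference between the two groups or pretreatment and posttreatment within one group". It then adds: "Analysis of covariance will be used to compare the differences of center effector other confounding factors". It does not say which visits are compared, and it names no method for several values from the same patient.

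**Missing data.** Under Withdrawal, dropout, and discontinuation: "Intention-to-treat analysis will be performed on missing data from discontinuers with the last observation carried forward method".

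**Role of the scores.** CAT, MMRC and TCM symptom score are secondary outcomes; under Main outcome measures the primary outcome is the frequency of exacerbations.

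**The concern.** The tests named each compare two groups or two times, and the covariance analysis is aimed at centre and confounders. Applied as written to these scores, they either rest each comparison on one visit or turn the visits into separate tests, each at P < 0.05. The patients are selected for high exacerbation risk, so some week 24 visits may fall in or near an exacerbation, and a single visit then carries that patient's result. For patients who leave, LOCF puts an early score in the place of the week 24 score.

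At stake is precision on symptoms and quality of life, and the credibility of the week 24 estimate under dropout, in a trial whose Discussion concedes that it adopted the minimum sample size. The repeated values will be collected in any case.

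**Working it through.** **Inputs from the protocol article.** Visits every 4 weeks: 24/4 = 6 post-baseline values by week 24 and 52/4 = 13 by week 52. Dropout of 20% over the course of the study; 50 patients per group.

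**Assumptions.** The article gives no SD, within-patient correlation or power for these scores, so there is no figure of its own to reproduce (its sample size calculation concerns exacerbations only). I assume unit variance at each visit and either an equal correlation r of 0.5 to 0.7 between all visits, or a correlation decaying as a^(visits apart) with a of 0.7 to 0.9 per 4 weeks.

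**Step 1: week 24 contrast, complete data.** With visit-specific treatment effects, the mixed model's week 24 contrast has the same variance as baseline-adjusted covariance analysis at week 24. For r = 0.6 and 50 per group both are 2 × (1 − 0.6²)/50 = 0.0256. The gain is 0%.

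**Step 2: average of weeks 12, 16, 20 and 24 against week 24 alone, both adjusted for baseline.**

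- Equal correlation: ratio = [(1 + 3r)/4 − r²]/(1 − r²).
- Decaying correlation: ratio = [(1/16) Σ Σ a^|i−j| − (mean of a^j)²]/(1 − a^12), with i and j running over visits 3 to 6.
- Power, if week 24 alone has 50% and the effect is constant from week 12: Φ(1.96/√ratio − 1.96).
- Effect growing linearly to week 24: the average effect is (3 + 4 + 5 + 6)/24 = 0.75 of the week 24 effect, so the test statistic is multiplied by 0.75/√ratio.

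| Correlation | Week 24 variance | Average's variance | Ratio | Power if constant | Statistic if linear |
|---|---|---|---|---|---|
| equal 0.5 | 0.750 | 0.375 | 0.50 | 79% | ×1.06 |
| equal 0.6 | 0.640 | 0.340 | 0.53 | 77% | ×1.03 |
| equal 0.7 | 0.510 | 0.285 | 0.56 | 75% | ×1.00 |
| decaying 0.7 | 0.986 | 0.631 | 0.64 | 69% | ×0.94 |
| decaying 0.8 | 0.931 | 0.631 | 0.68 | 66% | ×0.91 |
| decaying 0.9 | 0.718 | 0.488 | 0.68 | 66% | ×0.91 |

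So the average has 32% to 50% lower variance, but under linear growth the statistic moves between −9% and +6%.

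**Step 3: week 24 contrast with dropout.** Assume that 20% leave by week 24, with one sixth of them last seen at each of weeks 0, 4, 8, 12, 16 and 20. Let S_k be the baseline-adjusted covariance matrix of the first k post-baseline visits, and p_k the share of patients seen up to visit k. The model's week 24 variance is the last diagonal element of [Σ p_k S_k⁻¹]⁻¹, with each S_k⁻¹ padded with zeros to six visits. Completers' covariance analysis has the week 24 variance divided by 0.8. The ratios are 0.967, 0.960 and 0.954 (equal 0.5, 0.6, 0.7) and 0.967, 0.950 and 0.930 (decaying 0.7, 0.8, 0.9): a reduction of about 3% to 7%.

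**Step 4: LOCF under the same dropout.** With linear growth, a patient last seen at visit k contributes k/6 of the week 24 effect. The share kept is 0.8 + 0.2 × (0 + 1 + 2 + 3 + 4 + 5)/36 = 0.883, about 88%. If the effect is already constant from week 4, only those with no post-baseline value lose it: 0.8 + 0.2 × 5/6 = 0.967.

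**Step 5: milder dropout.** If the 20% is spread over all 13 visits, 0.20 × 6/13 = 9.2% leave by week 24. The reduction in Step 3 becomes about 1% to 3%, and the share kept in Step 4 becomes 0.908 + 0.092 × 0.417 = 0.946.

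**The case against.** The strongest reply is that this is a condensed article, and that the longitudinal model for secondary scores usually sits in a full protocol or analysis plan, which is not shown. That limits the point but does not remove it. The section does not defer to another document; it names methods, and those methods do not match the schedule. A fuller plan, if there is one, may already settle it.

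Several stronger readings are tempting and are not supported:

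- *That most of the collected scores go unused.* The article does not say which visits are tested. LOCF draws on earlier visits for discontinuers, and the 4-weekly visits also serve exacerbation counts and adverse events. What can be said is that no stated method uses the values jointly.
- *That the two-group or pre/post test is the only comparison.* Covariance analysis is also named, though not as a method that combines visits.
- *That a third to a half of the attainable variance reduction is lost.* The 32% to 50% in Step 2 is something else: the fall in variance relative to baseline-adjusted week 24. The share of attainable reduction lost by a single baseline-adjusted visit, measured against the average of all six visits with equal correlation, is 62%, 48%, 34%, 21% and 9% for r = 0.5 to 0.9. No single figure can be drawn from the documents.
- *That averaging is a free gain.* It changes the target from the end-of-treatment difference to a weeks 12 to 24 average. The article stresses weeks 24 and 52 and says nothing about time to effect, so making the average the main contrast is a trade-off for the trialists and not a correction.

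Two technical objections stand and shape the fix. MMRC is a 0 to 4 grade, so a Gaussian model is doubtful for it. An unstructured covariance over 13 visits has 13 × 14/2 = 91 parameters for 100 patients.

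**Conclusion.** The point holds as a modest, low-cost improvement for secondary outcomes. The stated methods do not use the 4-weekly scores jointly, and LOCF is a poor way to bring in discontinuers' earlier visits. At week 24 the benefit is confined to dropout: about 3% to 7% lower variance than completers' analysis if 20% leave by week 24 (about 1% to 3% if the 20% is spread over the whole study), and no LOCF attenuation, which would leave about 88% (or 95%) of a linearly growing effect. The larger reduction of 32% to 50% belongs to the weeks 12 to 24 average and turns into power only if the effect is constant from week 12.

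All these sizes rest on assumed correlations and dropout patterns, and the model's week 24 estimate assumes that dropout is explained by the observed scores (missing at random). A single-visit comparison with complete data is not invalid, and the conclusion on exacerbation frequency is untouched.

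**What to change.** Before unblinding, state for the between-group analysis of these scores:

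- **CAT and TCM symptom score:** one mixed model for repeated measures per outcome, with baseline value, visit, treatment, treatment-by-visit and within-patient correlation. The main contrast is the group difference at week 24, with week 52 supportive. Use the observed values without LOCF.
- **Weeks 12 to 24 average:** a supportive contrast from the same model, with a note that it helps if the effect is established by week 12 and may lose slightly if the effect is still growing.
- **MMRC:** an ordinal repeated-measures model, or keep a rank-based check beside the model.
- **Covariance:** name the structure and a fallback in advance, since an unstructured matrix over all 13 visits is heavy for 100 patients.

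Cost: some wording, slightly more analysis work in the SAS software already planned, and a covariance choice made in advance. No new visits, patients or data are needed.
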